# Multicenter study of lumen-apposing metal stents with or without pigtail in endoscopic ultrasound-guided biliary drainage for malignant obstruction—BAMPI TRIAL: an open-label, randomized controlled trial protocol

**DOI:** 10.1186/s13063-022-06106-1

**Published:** 2022-02-25

**Keywords:** Biliary drainage, Choledochoduodenostomy, Endoscopic ultrasound, Lumen-apposing metal stent, Malignant biliary obstruction, Plastic stent, Trial

## Abstract

**Background:**

It is unclear whether the insertion of an axis-orienting double-pigtail plastic stent (DPS) through biliary lumen-apposing meal stent (LAMS) in EUS-guided choledochoduodenostomy (CDS) improves the stent patency. The aim of this study is to determine whether this technical variant offers a clinical benefit in EUS-guided biliary drainage (BD) for the management of distal malignant biliary obstruction.

**Methods/design:**

This is a multicenter open-label, randomized controlled trial with two parallel groups. Eighty-four patients with malignant biliary obstruction will undergo EUS-BD (CDS type) using LAMS in 7 tertiary hospitals in Spain and will be randomized to the LAMS and LAMS plus DPS groups. The primary endpoint is the rate of recurrent biliary obstruction, as a stent dysfunction parameter, detected during follow-up. Secondary endpoints: technical and clinical success (reduction in bilirubin > 50% within 14 days of stent placement), safety, and others (number of reinterventions, time to biliary obstruction, prognostic factors, survival rate).

**Discussion:**

The BAMPI trial has been designed to determine whether the addition of a coaxial axis-orienting DPS through LAMS is superior to LAMS alone to prevent stent dysfunction.

**Trial registration:**

ClinicalTrials.govNCT04595058. Registered on October 14, 2020.

**Supplementary Information:**

The online version contains supplementary material available at 10.1186/s13063-022-06106-1.

## Main text

### Background

Transpapillary stenting by endoscopic retrograde cholangiopancreatography (ERCP) remains the gold standard treatment for malignant biliary obstruction (MBO), but may fail in up to 15% of cases, and it carries the risks of post-ERCP pancreatitis and stent dysfunction secondary to tumor ingrowth and/or overgrowth [1, 2]. For these reasons, since the emergence of Endoscopic Ultrasound-guided biliary drainage (EUS-BD) using electrocautery-enhanced (EE) lumen-apposing metal stents (LAMS), by creating a choledochoduodensotomy (CDS), it has been proposed as a viable alternative to ERCP [3, 4]. Firstly, as a rescue strategy after failed ERCP, in palliative scenarios, or even as a bridge to surgery [5, 6], and then recently, as a first-line modality for MBO in controlled trials [2, 7–9].

Although recent metanalyses and systematic reviews [10–14] have postulated that EUS-BD using LAMS has high technical and clinical success rates, some concerns exist regarding its safety, as non-negligible rates of adverse events (AE) have been reported [15, 16]. Recurrent biliary obstruction (RBO), as a stent dysfunction parameter, is a major issue to consider after EUS-BD using LAMS. Several cases of stent dysfunction (e.g., food or lithiasis impaction, sump syndrome, stent migration) have been documented due to a possible limitation in LAMS design, as the short length of the stent causes the distal flange to become impacted against the opposite biliary wall [10, 17, 18]. The insertion of a coaxial double-pigtail plastic stent (DPS) has been demonstrated to improve LAMS patency and bile flow, by maintaining a vertical orientation in the bile duct. But a recent retrospective study by our group did not encounter sufficient evidence to recommend its routine use [19].

For these reasons, a multicenter randomized controlled trial has been designed to assess whether a coaxial DPS within a biliary LAMS is superior to a single LAMS in EUS-BD (CDS type) for MBO.

### Methods/design

The BAMPI (*B*iliary *A*pposing *M*etal *PI*gtail) trial is a multicenter, open-label, randomized controlled clinical trial with two parallel groups, and with a 1:1 allocation ratio. Eighty patients with MBO will be scheduled for EUS-BD in seven tertiary Spanish hospitals and will be randomized to the LAMS alone or the LAMS plus DPS group. We hypothesize the addition of a prophylactic DPS through LAMS to be associated with fewer episodes of RBO and, consequently, fewer biliary reinterventions (BRI).

Central ethical approval of the study protocol has been confirmed by the Comité Ético de Investigación Clínica (CEIC) del Hospital Universitari de Bellvitge-IDIBELL (ref approval no. ICPS024/20, on November 2020) and we will not begin recruiting at other centers in the trial until local ethical approval has been obtained.

A checklist with the recommendations for Interventional Trials (SPIRIT) is attached as Additional file 1: SPIRIT-figure with schedule of enrolment, interventions, and assessments in the BAMPI trial (Fig. 1).

**Fig. 1 Fig1:**
[figure not shown]
Enrollment, interventions, and assessment in the BAMPI trial (SPIRIT-Figure). ªMandatory only in case of NOT meeting clinical success criteria on a previous visit (14 days).BRI biliary reintervention; d days; EUS-BD, endoscopic ultrasound-guided biliary drainage

#### Study population: Patient identification and consent

All patients admitted with distal MBO and clinical criteria that justify EUS-BD will be considered for consent. The investigator at each participating center will identify potential patients and will assess the inclusion of the patient in the study, and eligibility either as a first-line BD method, or as a rescue method after failed ERCP. The patient will be correctly informed by personnel knowledgeable about the specifics of the study, who will help to resolve any questions that may arise. The informed consent form will be signed prior to the procedure and a signed copy will be given to the patient. The patient has the right to opt out of the study at any time.

The inclusion and exclusion criteria are listed in Table 1.

**Table 1 Tab1:** Inclusion and exclusion criteria

**Inclusion criteria:** **Patients eligible for the trial must fulfill all the following at randomization** - Age 18 years or more. - Malignant biliary obstruction with clinical criteria that justifies EUS-guided biliary drainage. - Capable of understanding and signing informed consent form. - Understanding the type of study and complying with the follow-up of complementary tests during the study’s duration.	
**Exclusion criteria:** **Patients with any of the following will be excluded** - Pregnancy or breast-feeding. - Severe coagulation disorder: INR > 1.5 not correctible with administration of plasma and/or platelets < 50,000/mm3. - Maximum cross diameter of the CBD < 10 mm. - Another type of biliary drainage at the time of the procedure (cholecystostomy, percutaneous drainage, etc.). - Failure to sign informed consent form. - Intellectual handicap and unable to understand the nature and possible consequences of the study, unless there is a competent legal representative. - Unable to adhere to subsequent follow-up requirements.	

*CBD* common bile duct, *EUS* endoscopic ultrasound, *INR* international normalized ratio

#### Recruitment

Principal investigators from each center will have the task of presenting strategies to promote enrolment and ensure the target sample size. Prior to the start of the study, a meeting with oncology and digestive surgery teams will be organized with the aim of creating collaboration bridges.

#### Randomization and masking

Patients will be enrolled in this trial by gastroenterologists, surgeons, oncologists, and endoscopists who will evaluate cases in the inpatient wards or outpatient consultation areas. Investigators of each center will be responsible for entering all necessary criteria to an online platform that will generate the randomization sequence, and participants will be randomized with an arbitrary number.

A code list will be generated by our biostatistics department, using R software (v 3.6.3) by randomization with a 1:1 randomization ratio, by blocks, stratified by age (< 65 years old/> 65 years old) and by the presence of liver metastases. The assumption is made that liver metastasis may elevate bilirubin and cholestasis parameters without involving bile duct obstruction. Everyone will be assigned a randomization code along with the treatment that corresponds to it. Once the patient meets the eligibility criteria and has provided informed consent, we will proceed to the allocation of each participant centrally, ensuring allocation concealment, and based on the randomization list. To prevent different subject recruitment rates at the various hospitals from interfering in the development of the study, the entire population will be randomized in blocks of four between the two treatment possibilities.

#### Procedural technique

##### Qualification of centers

This clinical trial will be performed at the endoscopy unit of seven referral centers in Spain. Endoscopists will all be experienced in endoscopic intervention and therapeutics, such as stenting and EUS-guided transmural drainage. To avoid biases derived from the learning curve, only those centers with proven experience using biliary EE-LAMS (EUS-guided CDS) have been invited to participate. To objectify usage data, the database “NRPAL: National Registry of Lumen Apposing Metal Stents Incidences, NCT04059926”, which collects data from all LAMS placed for 1 year, was checked. Minimum requirements were at least 12 LAMS placed in one year for any indication and a minimum experience of 7 EUS-BD using EE-LAMS. All the experienced endoscopists are members of the Spanish Society of Digestive Endoscopy (SEED).

##### General description of the technique

Treatment allocation is to EUS-BD with LAMS alone vs. LAMS plus DPS. All procedures will be performed by experienced endoscopists in EUS-guided transmural stenting. Procedures will be performed under deep sedation or tracheal intubation, in accordance with the directives of each center. Coagulation disorders will be corrected prior to the procedure. In case of INR > 1.5, this will be corrected with the protocol of each institution. In all interventional procedures, CO2 will be used as an insufflation agent. Prophylactic antibiotic therapy will be given in accordance with institutional protocols.

##### EUS-BD with EE-LAMS

Each selected case will ensure a conclusive diagnosis of MBO. If necessary EUS-guided tissue acquisition (TA) will be performed previously to or immediately after the transmural drainage. The TA technique will be at the endoscopist’s choice. Firstly, EUS oversight will be done with the purpose of ruling out features that could jeopardize a transmural BD (such as ascites, long distance common bile duct (CBD)-transducer, or intervening vessels). The extrahepatic bile duct will be identified by using a linear echoendoscope (Fujifilm EG-580-UT, Olympus GF-UCT180), selecting an optimal point for carrying out the EUS-guided intervention. The long scope position will preferably be used to maintain stability and, if necessary, to ease advancing of a guidewire to intrahepatic direction. A small-medium sized LAMS (6, 8, and 10 mm in diameter and 8 or 10 mm in length, Hot-AXIOS™ stent with an electrocautery-enhanced delivery system, Boston Scientific, Marlborough, MA, USA) will be used in all included cases.

The access step will be standardized in two different techniques, as explained in our previous report [19]: (i) freehand style (optional preloaded guidewire), with direct access to the bile duct, and (ii) classic technique, with initial puncture of the extrahepatic bile duct using a 19-gauge needle and advancing a standard guidewire, after which a LAMS is advanced over the guidewire.

In all cases, the biliary LAMS is inserted using the cautery system, and deployed under EUS-guidance without tract dilation. The use of fluoroscopy will be decided upon based on technical considerations and the endoscopist’s opinion.

Selection of LAMS size will be based on bile duct diameter and availability.

##### LAMS plus coaxial DPS procedure

In those patients allocated in the LAMS-DPS cohort, a DPS (preferably 7Fr × 3, 5 or 7 cm, Advanix, Boston Sc) will be placed coaxially through the LAMS, preferably with upward (intra-hepatic) orientation. This selection of small DPS sized should ease the advance and release by offering less friction.

##### Additional interventions

After the LAMS deployment, intra-stent dilation is permitted using balloons at the endoscopist’s discretion.

Other endoscopic procedures such as EUS-guided TA, EUS-guided gastro-enterostomy, stenting (esophageal, duodenal), and EUS-guided celiac plexus blockage/neurolysis performed during the index procedure will be meticulously noted in a specific section in the electronic case report form (eCRF).

##### Gallbladder option

When a CDS is not possible or too risky, a BD rescue by EUS-guided gallbladder transmural drainage may be considered. It is important to note that this should only be offered in cases without an optimal endosonographic window for the creation of CDS (e.g., interposal vessels, CBD < 10 mm, excessive GI tract-CBD distance, scope instability, others). It may be randomized in the same way (LAMS vs. LAMS-DPS group) and followed up according to the protocol. This additional subgroup will be analyzed and documented, but outside of the trial’s main outcomes.

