#### Statistical analysis

Statistical analysis will be carried out with the R statistical software (version 3.6.2) supervised by the Biostatistics team of our research institute (IDIBELL).

Intention-to-treat and per-protocol analysis will be carried out. All study variables will be presented for stent groups and in total, using descriptive statistics in accordance with the nature of the variable. Thus, continuous variables will be described indicating the number of non-missing observations, mean, standard deviation, minimum, first quartile, median, third quartile, and maximum. The categorical variables will be described indicating the number of non-missing observations and the percentages of the different categories.

Realization of the aim of the study will be analyzed by comparing the cumulative incidence of RBO (as a stent dysfunction parameter) in the LAMS cohort versus LAMS-DPS cohort using a Chi-Square test. The magnitude of the effect will be estimated through an incidence ratio and relative risk with 95% confidence interval. The main analysis will be replicated in an adjusted way using a binomial regression model. Age, sex, oncological status, and comorbidities will be taken as adjustment variables.

Safety will also be evaluated by describing the number and type of AE in each study group, and the incidence will be compared using a chi-square test. In addition, the survival of patients will be analyzed according to the two proposed strategies until the end of follow-up, describing the Kaplan-Meyer curves and comparing them using the LogRank test. The level of statistical significance is established at *p* value < 0.05.

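### Gallbladder-drainage cases may be randomised yet sit outside the main outcomes; if allocation precedes the EUS window check, this is a post-randomisation exclusion that conflicts with intention-to-treat

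*Protocol article*

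**What the plan says.** The Gallbladder option section offers transmural gallbladder drainage as a rescue when a CDS is not feasible or carries too much risk. It limits the option to cases without a good endosonographic window, with examples that end openly: "e.g., interposal vessels, CBD < 10 mm, excessive GI tract-CBD distance, scope instability, others". On allocation it says: "It may be randomized in the same way (LAMS vs. LAMS-DPS group) and followed up according to the protocol". On analysis it says: "This additional subgroup will be analyzed and documented, but outside of the trial’s main outcomes".

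Four other places bear on this:

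- **Randomization and masking:** "Once the patient meets the eligibility criteria and has provided informed consent, we will proceed to the allocation of each participant centrally".
- **EUS-BD with EE-LAMS**, on the index procedure: "Firstly, EUS oversight will be done with the purpose of ruling out features that could jeopardize a transmural BD".
- **Statistical analysis:** "Intention-to-treat and per-protocol analysis will be carried out". No exception is made for gallbladder cases.
- **Table 1, exclusion criteria:** "Maximum cross diameter of the CBD < 10 mm".

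The Study population section has consent signed before the procedure, and Methods/design describes the trial as open-label. Trial status shows that the option came in with amendment 2 (November 2021), a year after recruitment began on November 17, 2020.

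**The concern.** An intention-to-treat comparison is protected because nothing that happens after allocation decides who is counted. Here a rule in the protocol takes a group of patients who may carry a trial allocation out of the main outcomes. If allocation comes before the endoscopist inspects the window, membership of the primary comparison depends on a later judgement. The criteria for that judgement are partly subjective and not closed, and no section withholds the arm until it has been made. Conversion could then differ between arms, and patients with difficult anatomy could be removed unevenly.

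This is not a detail left to an unseen analysis plan. The protocol states the exclusion and also states an analysis principle that, under one order of events, does not allow it.

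There is a separate eligibility problem. A common bile duct under 10 mm keeps a patient out of the trial in Table 1, yet it is a listed reason for the gallbladder option in patients who may be randomised.

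**Working it through.** **1. Order of events.** No section says whether allocation precedes the EUS inspection, or whether a switched patient keeps an earlier allocation.

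*Pointing to allocation first:*
- Consent precedes the procedure, allocation follows eligibility and consent, and nothing makes allocation wait for EUS.
- The window is checked at the start of the EUS procedure.
- The option is called a rescue.
- Scope instability can be judged only with the scope in place.

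*Pointing to randomisation after the switch:*
- The wording says that such a case may be randomised, not that it remains in its arm.
- The cases are called an additional subgroup.
- Patients with a bile duct under 10 mm are excluded by Table 1, so they could enter only as a side cohort.

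The first order is likelier but not stated. Under it, the Gallbladder option and Statistical analysis sections conflict. Under the second they do not.

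**2. The plan's own sample size.** Inputs from Sample size calculation: p1 = 0.20, p2 = 0.01, two-sided alpha 0.05, power 0.80. Pooled-variance formula without continuity correction:

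n = [z(0.975)·√(2·p̄·(1−p̄)) + z(0.80)·√(p1(1−p1) + p2(1−p2))]² / (p1−p2)²

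- p̄ = 0.105, √(2 × 0.105 × 0.895) = 0.4335, √(0.16 + 0.0099) = 0.4122
- n = (1.960 × 0.4335 + 0.8416 × 0.4122)² / 0.0361 = 39.7, so 40 per arm, as stated
- Dropout: 80 × 1.05 = 84, as stated

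**3. Power if patients leave the primary analysis.** Power = Φ{[0.19·√n − 1.960 × 0.4335] / 0.4122}. The share leaving is not in the documents; 0 to 20% is an assumed range.

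| Share leaving | n per arm | Power |
|---|---|---|
| 0% | 40 | 80.3% |
| 5% | 38 | 78.2% |
| 10% | 36 | 75.9% |
| 15% | 34 | 73.4% |
| 20% | 32 | 70.8% |

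**4. What unequal exclusion could do (assumed values only).** Let the true rate of recurrent biliary obstruction (RBO) be 20% in both arms. Let the excluded patients have risk r, and let a share g of an arm be excluded. The observed rate is (0.20 − g·r)/(1 − g).

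- r = 0.40, g = 5% in one arm: (0.20 − 0.02)/0.95 = 18.9%
- r = 0.40, g = 15% in the other: (0.20 − 0.06)/0.85 = 16.5%
- Relative risk 16.5/18.9 = 0.87 with no true effect. For r from 0.30 to 0.50 it runs from 0.94 to 0.80. With the arms reversed it runs from 1.07 to 1.25.
- Equal exclusion (10% in each arm) leaves the relative risk at 1.0.

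This shows only that the bias can go either way and vanishes when exclusion is balanced. It does not estimate the bias in this trial.

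**The case against.** The strongest defence is that the text can be read as describing a side cohort, randomised after the switch and reported apart from the trial. Nothing is then excluded after randomisation. That reading is open, and a reader who infers that switched patients keep an earlier allocation goes beyond the text. The same holds for the inference that the deciding endoscopist knows the arm: it is plausible in an open-label trial with no fixed allocation time, but no section says so.

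The defence can also say that the option is limited to cases without a good window, that most listed reasons are anatomical, and that both arms follow the same steps until the LAMS is in place. Knowing that a pigtail is to follow does not change the anatomy. This weakens the case for a large bias. It does not remove the problem, because the criteria include a judgement of risk and an open end.

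A reader might further infer that gallbladder cases use up the 84 patients and that the trial loses its power. No section says that they count towards the 84, and at 5% loss the fall is about two percentage points.

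Finally, a remedy that treats future and past patients differently mixes two populations. That is true, and it is why the CDS-only analysis belongs beside the primary one.

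**Conclusion.** The point holds in conditional form. The protocol lets gallbladder cases be randomised, puts them outside the main outcomes and promises intention-to-treat without exception, and it does not fix the order that decides whether these statements agree. If allocation comes first, which is likelier on the text, the rule is a post-randomisation exclusion and conflicts with intention-to-treat. If randomisation follows the switch, there is no conflict, but the protocol should say so.

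The documents do not support the stronger statement that the randomised comparison has been compromised. The conversion rate, its balance between arms and the direction of any bias are all unknown. The stated sample size reproduces and is not disputed. The power loss from 80.3% to 78.2% rests on an assumed 5% loss in each arm and is a lesser matter than the definition of the analysis set.

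The double use of a bile duct under 10 mm, as an exclusion criterion and as a reason for the option, needs reconciling whichever order applies.

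**What to change.** (a) For patients still to be enrolled, release the allocation only after EUS has confirmed a CDS window, and at the latest once the LAMS is deployed, since the arms share the steps up to there. List gallbladder cases as a separate cohort that does not count towards the 84.

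(b) For any patient allocated before a switch to the gallbladder, keep that patient in the allocated arm in the intention-to-treat primary analysis. Report the CDS-only result as a sensitivity analysis.

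(c) Reconcile Table 1 with the Gallbladder option section on a bile duct under 10 mm.

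The cost is one protocol amendment and a later allocation step on the existing online platform. Two limits apply. If allocation waits until the LAMS is deployed, success of that shared step is no longer compared between arms. And with recruitment due to finish in October 2022, part (a) reaches only the patients not yet enrolled, so part (b) is needed for the rest. The Statistical analysis plan section bars changes once the database is closed, so the amendment must come before then.

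No stated figure changes: 84 randomised less 5% dropout (84 × 0.95 = 79.8) still leaves about 40 per arm.
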